### Mortality

Mortality (time to death) will be analysed using Kaplan-Meier curves and Cox proportional hazard models, both unadjusted and adjusting for previously described covariates. Individuals who did not experience an event (death) will be censored at the end of the follow-up period of the study. Individuals withdrawn from the study early or lost to follow-up will be censored at the date of withdrawal or the last contact visit respectively. Results will be presented using hazard ratios and 95% confidence intervals for relative comparisons between the groups and absolute risk and differences will be estimated at both 28 and 90 days.

### Costing analysis

The cost of ICU care has been estimated at $4375 [15] and $5534 (Medical Division SCGH, 2015) per day based on national and state data respectively. From these figures, any reduction in costs through reduced LOS will be calculated. The cost per melatonin dose ($20 AUD per 30 ml bottle of 2 mg/ml) as well as consumables (syringe for NGT application) will also be calculated. There would also be a small ‘time’ cost associated with administration, but we believe it could reasonably be included in the general nursing workload. Costs will be presented in Australian dollars, adjusted to 2020.

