## Study methods

This is a multi-centre, randomised, double-blinded, placebo-controlled trial of melatonin versus placebo to decrease the rate of delirium in ICU. A total of 850 ICU patients have been randomised on a 1:1 ratio to receive either melatonin or a placebo. Study participants were administered an oral dose of melatonin 4 mg enterally or placebo once daily at 21:00hs. for up to 14 days or until discharge from the ICU. Participants were monitored twice daily for symptoms of delirium. Additionally, data is being collected on the duration and severity of delirium, sleep quality, hospital and ICU length of stay (LOS), duration of mechanical ventilation, and mortality.

Patients were randomised according to a computer-generated randomisation list, stratified by site, with standard block sizes of 6. Variable block sizes were considered unlikely to provide additional benefit, as the study drug and placebo have the same appearance and all clinical staff are blinded, thus maintaining allocation concealment. The randomisation list has been maintained by the University of Western Australia Centre for Applied Statistics.

The patients, investigators, ICU doctors, and nurses looking after patients enrolled in the study are blinded to the treatment that the patients are receiving. Only the University of Western Australia Centre for Applied Statistics, the compounding pharmacy, and the independent Data Safety Monitoring Committee (DSMC) (should they need to, in order to investigate an adverse event) have had access to the treatment allocation list.

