Based on the sample size calculations, with an alpha value of 0.05 and a power of 80%, a total of 850 patients have been recruited to the study, with 425 patients in each arm. Estimates of sample size were made based on the percentage of delirium-free assessments (the primary outcome) and, secondarily, the ICU LOS. LOS was chosen in addition to the percentage of delirium-free assessments as a significant relationship between delirium and LOS has been observed. Delirium assessment is by its nature subjective and the investigators wished to also allow the study to be powered to detect a reduction of LOS of 1 day (as an objective patient-orientated outcome). An audit of 100 patients across the two primary sites was used to provide preliminary data to guide sample size calculations where an average of 54% of assessments were deemed delirium free (standard deviation of ± 45%). The research group is interested in being able to detect a 10% increase in the percentage of delirium-free assessments. This would require a sample size calculation of 319 per group. Adjustment for non-parametric data (15%) increases this to 367 per group. It is expected that up to 10% of patients recruited in the study will not be assessable for delirium at any point during the study. To account for this, and missing data/loss to follow-up, the sample size was increased by 15% to 423 patients per group (total rounded to 850).

To detect a change in LOS of 1 day, using a sample size calculation for a gamma distribution, 387 patients per group would be required. The greater number of 850 was selected to have enough power to answer both questions. The formula used to calculate sample size was that described by Wand and Chow in 2007 [27].

The framework of the study is of superiority of melatonin over placebo for the prevention of delirium. Superiority analyses will be two-sided and considered statistically significant at the 5% level.

The DSMC is comprised of an independent intensivist, an epidemiologist, and a statistician independent of the trial statistician. The independent DSMC will review all serious adverse events and perform an interim analysis after 400 patients using the Haybittle-Peto stopping rule. The Haybittle-Peto stopping rule states that if an interim analysis shows a probability of equal to or less than 0.001 that a difference as extreme or more between the treatments is found, given that the null hypothesis is true, then the trial should be stopped early [28].

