### ICU and hospital length of stay

Initial comparisons between the two groups for ICU and hospital length of stay will be compared using Student’s *t* test. Supporting analysis will also be carried out using Poisson regression, accounting for previously described covariates. Length of stay will be analysed in particular with the aforementioned subgroups.

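### The costing values shorter stay at the full ICU day price with no offset for ward days that may replace it, so it gives a gross ICU bed-day saving, not a net hospital saving

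*SAP article*

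**What the plan says.** The Costing analysis section of the SAP article begins with its bed-day prices: "The cost of ICU care has been estimated at $4375 [15] and $5534 (Medical Division SCGH, 2015) per day", from national and state data respectively. The rule follows: "From these figures, any reduction in costs through reduced LOS will be calculated". On the cost side, the sentence opening "The cost per melatonin dose ($20 AUD per 30 ml bottle of 2 mg/ml) as well as consumables (syringe for NGT application) will also be" adds drug and consumables to the sum. Nursing time for administration is considered and set aside, because "we believe it could reasonably be included in the general nursing workload". No price is given for a day outside the ICU, and the section does not say whether its result is a cost to the ICU or to the hospital.

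Elsewhere the article treats the two stays as separate outcomes. Under ICU and hospital length of stay it says: "Initial comparisons between the two groups for ICU and hospital length of stay will be compared using Student’s" *t* test. The Analysis section lists the economic analysis as the sixth secondary outcome. Study methods says the investigators also wanted the trial "powered to detect a reduction of LOS of 1 day".

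**The concern.** A patient who leaves the ICU a day earlier does not usually leave hospital a day earlier. If that day is spent on a ward, the hospital avoids the ICU price less the ward price. The stated rule credits the full ICU price.

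The error runs in one direction and arises in the scenario the trial was also sized for, a one-day reduction in stay. A shift of care from ICU to ward would be reported as if the whole ICU day had been saved. The data needed to avoid this are already collected: hospital days minus ICU days gives the non-ICU days for each patient.

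**Working it through.** The article states no saving, so there is no figure of the plan's to reproduce. The check asks what its rule credits and what remains once ward days are charged.

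**Inputs from the SAP article**
- ICU day price C: $4375 or $5534 (Costing analysis).
- Reduction in stay: 1 day (Study methods).
- Study drug: 4 mg once daily, "for up to 14 days or until discharge from the ICU" (Study methods), at $20 per 30 ml of 2 mg/ml (Costing analysis). One dose is 4/2 = 2 ml, costing 20 × 2/30 = $1.33. Fourteen doses cost $18.67, which is negligible beside C.

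**Assumptions, not in the documents**
- Ward day price W: $800 to $2000.
- Share r of avoided ICU days that become ward days: 0 to 1.

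**Overstatement per ICU day avoided, before drug and consumables**
- Saving credited by the rule = C.
- Saving net of ward care = C − rW.
- Overstatement = rW / (C − rW).

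With r = 1 (hospital stay unchanged):

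| Ward day W | Net saving at $4375 | Overstatement | Net saving at $5534 | Overstatement |
|---|---|---|---|---|
| $800 | $3575 | 22% | $4734 | 17% |
| $1000 | $3375 | 30% | $4534 | 22% |
| $1500 | $2875 | 52% | $4034 | 37% |
| $2000 | $2375 | 84% | $3534 | 57% |

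With r = 0.5 and the same ward prices, the overstatement at $4375 runs from 400/3975 = 10% to 1000/3375 = 30%. At $5534 it runs from 400/5134 = 8% to 1000/4534 = 22%. With r = 0 (hospital stay falls as much as ICU stay) it is 0%. Outside the assumed price range and with r = 1, a $500 ward day gives 13% and 10% at the two ICU prices, and a $2500 ward day gives 133% and 82%.

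**When the sign changes**

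Suppose ICU stay falls by 1 day and total hospital stay rises by k days. Ward days then rise by 1 + k, and hospital cost rises if (1 + k)W > C, that is, if k > C/W − 1.
- $4375 and W = $1500: k > 1.92.
- $5534 and W = $1500: k > 2.69.
- Across the assumed prices: from k > 4375/2000 − 1 = 1.19 to k > 5534/800 − 1 = 5.92.

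**Invented records to show the mechanism (ICU days/hospital days)**
- Placebo 8/20, melatonin 7/20: the rule credits $4375. Ward days are 12 and 13, so at W = $1500 the net saving is $2875.
- Placebo 8/20, melatonin 7/23: the rule again credits $4375. Ward days are 12 and 16, so at W = $1500 hospital cost is 4 × 1500 − 4375 = $1625 higher. The break-even ward price is 4375/4 = $1094.

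**The case against.** The strongest reply concerns perspective. The section opens with the cost of ICU care, and from the ICU's own budget, ICU days times the ICU day price is the right sum with no ward offset. On that view the only fault is that the perspective is unstated. The reply has force, but the section declares no ICU-only perspective and describes its result simply as a reduction in costs, which a reader will take as money saved on the patient's care.

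A second reply is that the article is condensed, and its additional files and the protocol are not shown. A list of unit costs could well sit there. But the section goes beyond leaving a list out: it names its bed-day prices and says the saving is calculated from them. The criticism applies to that stated rule.

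Third, the economic analysis is the last of six secondary outcomes and affects neither the primary comparison nor safety. Hospital stay is also reported, so a rise would be visible beside the costing. Both points are correct, and they limit the consequence.

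Three stronger readings are tempting, and the documents do not support them:
- A reader might infer that the plan overstates the saving by a fixed 20% to 80%. That range needs one-for-one replacement and a ward day at about 17% to 44% of the ICU day price, and the documents give neither.
- A reader might infer that the rule is likely to show a saving when hospital cost rose. Replacing an ICU day with a cheaper ward day still saves money. Reversal needs hospital stay to lengthen while ICU stay shortens, and nothing in the article suggests that pattern.
- A reader might take LOS in this section to mean hospital stay, so that ward days are priced at the ICU rate. The term is not qualified there, but it follows directly after ICU prices, and the sample size text uses plain LOS for ICU stay. The ICU reading is the more natural one.

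**Conclusion.** The point holds in conditional form. As written, the costing gives a gross ICU bed-day saving, which exceeds the net hospital saving to the extent that avoided ICU days are spent on a ward. The percentages rest on two assumptions from outside the documents, the ward price and the replacement share, and should always be quoted with them. The direction does not depend on the ward price: with any replacement, the credited saving is too high as a measure of hospital cost. A wrong sign is possible only in the edge case described above. The issue is confined to a secondary outcome, but it should be corrected because the bias is built into the stated rule and is easily removed.

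**What to change.** Name the stay and the perspective in the Costing analysis section. For each patient compute:

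ICU days × ICU day price + (hospital days − ICU days) × ward day price + study drug and consumables.

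Report the between-arm difference in mean total cost with a bootstrap 95% CI, once under each of the two ICU prices. Cite a source for the ward price, express it in 2020 Australian dollars like the other costs, and repeat the analysis over a range of ward prices. The two sources for the ICU prices are not shown, so it cannot be assumed that either gives a ward price.

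If only the ICU figure is kept, label it a gross ICU bed-day saving and do not present it as a reduction in the cost of care.

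The cost is a wording change, one extra unit price to source and a short calculation on data already collected. The stated saving will probably be smaller. The article says it was submitted before database lock and unblinding, so at that stage the change could still be prespecified.

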### Missing data

Due to the nature and implementation of the CAM-ICU tool, it is expected there will be some missing data. However, such data is expected to be missing at random and consequently appropriate analyses will be carried out. The patterns of data availability for primary and secondary outcomes and reasons for missingness, where known, will be summarised for the two treatment groups. In situations where mixed modelling is the primary analysis, missing data will be handled by the likelihood-based estimation used in these analyses where the MAR assumption holds. In other situations of missing data, analyses will be carried out, if applicable, using multiple imputation.

It is expected that the source of missing data will be predominantly the dependent variable (based on missed delirium free assessments and outcomes). Consequently, we will not use multiple imputation techniques if this is the case and simply report the missingness patterns. However, if missing data is present in other variables, we will use these techniques, utilising the multiple imputation with chained equations (MICE) methodology [31].

### Harms

Safety will be evaluated by tabulation of adverse events and will be presented with descriptive statistics at baseline and follow-up visits for each treatment group. With each SAE, the study investigator will determine the intensity and causality as per ICH GCP guidelines All SAEs will be discussed at the Data Safety Monitoring Committee meetings to reach a consensus on causality. If this differs from the original decision the local ethics committee is informed.

The number and proportion of patients experiencing at least one AE, and the number and proportion of patients experiencing at least one SAE will be presented descriptively. The mean number of AEs and SAEs per patient will be presented. In addition, the frequencies of patients with (i) adverse events and (ii) serious adverse events will both be compared between the intervention groups using Fisher’s exact tests or chi-squared tests.

Data analysis will be carried out using the Stata MP, version 15. This SAP has been written in accordance with published guidelines for the content of statistical analysis plans in clinical trials [27].

## Trial status

At the time of publication, the ProMEDIC study had completed enrolment and follow-up of outcome data was ongoing. The statistical analysis plan of the study has been submitted for publication to this peer-reviewed journal before completion of follow-up and unblinding.

## Data Availability

There is no data from which conclusions have been made to accompany this manuscript.

## Abbreviations

CAM-ICU: Confusion assessment method for ICU
CAM-S: Confusion assessment method-severity
DSMC: Data safety monitoring committee
ICU: Intensive care unit
ITT: Intention to treat
LOS: Length of stay
PP: Per protocol
SAP: Statistical analysis plan
